## 2 Outcomes and Objectives

### 2.1 Primary

The primary objective of the TODAY trial is to compare the three treatment arms on time to treatment failure in patients enrolled from 10 to 17 years of age with T2DM. The study is analyzed as an 'intention to treat' study enrolling 750 patients (250 per arm). The study is powered to allow all three possible comparisons between the treatment groups while maintaining the overall significance level at 0.05. The three treatment group comparisons are: (1) metformin alone versus metformin plus intensive lifestyle program, (2) metformin alone versus metformin plus rosiglitazone, and (3) metformin plus intensive lifestyle program versus metformin plus rosiglitazone. Treatment failure is defined in one of two ways:

1. **HbA1c  $\geq$  8% over a 6-month period.** All regularly scheduled HbA1c values must be  $\geq$  8% over a 6-month period. If any one value is  $<$  8%, after which HbA1c re-elevates to  $\geq$  8%, the clock will restart at the time of the re-elevation. At least two consecutive measurements must be  $\geq$  8% over 6 months.
2. **Inability to wean from temporary insulin therapy due to metabolic decompensation.** Participants who experience metabolic decompensation requiring temporary use of insulin, who cannot safely be weaned from insulin within three months, will be classified as treatment failures (see section 4.7).

The primary outcome of treatment failure is defined in terms of HbA1c, because it correlates with glycemic control and long-term diabetes outcome. Because HbA1c is the primary outcome, investigators and patients are blinded to HbA1c values. In addition, patients with abnormal reticulocyte count or HbA1c chromatogram indicating the presence of abnormal hemoglobin variants other than heterozygosity for S and C at the time of initial screening are excluded from participation due to interference with HbA1c assays. Homozygous S and C and S/C patients are excluded. These patients are referred for appropriate hematologic evaluation. Management of patients with metabolic decompensation requires insulin treatment. However, if insulin treatment cannot be withdrawn after three months, this is considered a failure of the primary therapy.

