### 1.2 Overall Design and Study Interventions

The three treatment regimens are: (1) metformin alone, (2) metformin plus rosiglitazone, and (3) metformin plus an intensive lifestyle intervention called the TODAY Lifestyle Program (TLP). The study recruits patients over a three-year period and follows patients for a minimum of two years. Patients are randomized within two years of the diagnosis of T2DM. The primary outcome is time to treatment failure as defined below. The anticipated duration of the TODAY trial is seven years, including pre-trial planning and post-trial analysis and reporting.

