## 3 Recruitment, Screening, and Enrollment

### 3.1 Recruitment Goals and Strategies

The primary source of participants for the TODAY study is the active patient population of the study sites and their usual referral sources. Supplemental strategies for increasing referrals (such as presentations to local physician groups) are also utilized. Site-specific recruitment strategies are developed by each local study team. The period of recruitment is anticipated to last four years.

The TODAY sites were chosen partially based on the ethnic/racial composition of their patients with T2DM. It is estimated that the ethnic/racial distribution of enrolled participants will be 33% African American, 31% Hispanic (largely Mexican American), 12% Native American, 20% non-Hispanic White, and 4% other (largely Asian American). Study sites will develop targeted strategies for maximizing the recruitment of the particular racial and ethnic groups seen in clinic.

Recruitment efforts are integrated into and supported by other TODAY activities, including national and local public relations efforts, on-going development and adaptation of recruitment and advertising materials, and presentations at local and national meetings. Recruitment of current patients as well as community-based recruitment will begin in parallel from the start of the enrollment period.

Recruitment progress is monitored regularly by the coordinating center and the Recruitment and Retention Committee. Limited, anonymous data are collected on individuals who refuse to participate in order to tailor the recruitment process. Assistance is offered to clinical centers struggling with recruitment efforts.

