# 8 Statistical Considerations

## 8.1 Sample Size

The primary outcome for the TODAY study is time to treatment failure, defined as persistently elevated HbA1c levels ( $\geq 8.0\%$  for 6 months) or the inability to be weaned safely from temporary use of insulin therapy. No published data exist that allow estimation of the rate of occurrence. From unpublished data collected in the participating clinical centers, it is estimated that between 10-20% of children will have an HbA1c above the threshold by the end of each 6 month period, beginning at the end of the first year. The following assumptions were used to determine the sample size goal for TODAY:

- Primary outcome is time to failure as defined above.
- Eligible patients are randomized evenly to one of three treatment arms and followed for an additional two years following close of randomization.
- Rate of treatment failure within treatment group is constant over time.
- Treatment failure in the reference group (metformin alone) is at least 10% per six-month period, beginning at the first annual visit.
- There is a reduction of at least 40-50% in the treatment failure rate in one of the more intensively treated groups.
- Ten percent of patients are lost to drop-out during each 6 month period.
- The type I error rate ( $\alpha$ ) is 0.05 (two-sided) with a Bonferroni adjustment [Miller 1981] for three pair-wise comparisons of the three treatment groups.

Given these assumptions, if 10% of the metformin group has an HbA1c above the threshold, 250 participants per arm provides at least 90% power to detect a 50% reduction in the treatment failure rates in at least one combination therapy group (i.e., 5% with HbA1c above threshold during a six-month period). If 20% of the metformin group has an HbA1c above the threshold, 250 participants per treatment arm provides at least 90% power to detect a 40% reduction in hazard rates in at least one of the combination therapy groups (i.e., 12% failing during a six-month period). Therefore, 250 participants per group are recruited.

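### Section 2.1 calls all three comparisons powered, but section 8.1 supports power only for a combination arm against metformin; lifestyle versus rosiglitazone has much less if both arms work

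*Protocol*

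**What the plan says.** Section 2.1 of the protocol sets the size, "The study is analyzed as an 'intention to treat' study enrolling 750 patients (250 per arm", and then says: "The study is powered to allow all three possible comparisons between the treatment groups while maintaining the overall significance level at 0.05". It lists the pairs, the last being "3) metformin plus intensive lifestyle program versus metformin plus rosiglitazone".

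Section 8.1 holds the only power calculation. Alpha "is 0.05 (two-sided) with a Bonferroni adjustment [Miller 1981] for three pair-wise comparisons of the three treatment groups". The effect assumed is a 40-50% reduction in one of the two more intensive groups. For a metformin rate of 10% per six months, 250 per arm "provides at least 90% power to detect a 50% reduction in the treatment failure rates in at least one combination therapy group", that is, 10% v 5%. The second scenario is 20% v 12%, again with at least 90% power. Section 8.1 gives no rates, target difference or power for lifestyle versus rosiglitazone.

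The source of the planning rate is worded as a threshold: "it is estimated that between 10-20% of children will have an HbA1c above the threshold by the end of each 6 month period". The list of assumptions in the same section, however, gives the metformin rate as treatment failure, starting at the first annual visit.

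On accrual, section 1.2 says "The study recruits patients over a three-year period and follows patients for a minimum of two years", while section 3.1 says "The period of recruitment is anticipated to last four years". Section 8.1 adds two years after randomization closes but gives no accrual length.

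**The concern.** The sentence in 2.1 makes two claims: the type I error is controlled over three pairs, and the study is powered for three pairs. Section 8.1 supports the first for all pairs and the second only for those against metformin. Planning for a combination arm to beat metformin says nothing about how far the two combination arms will differ. If both deliver the planned reduction, their hazard ratio is 1.

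What is at stake is how the third comparison is read. A non-significant lifestyle versus rosiglitazone result would look like the outcome of a comparison planned with high power, and so like evidence that the two are similar. In the plausible case that both work to different degrees, the trial would usually miss the difference.

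Two smaller points touch the same calculation. The power statements use threshold wording for what is meant as confirmed failure, and the accrual period has two values.

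**Working it through.** **Inputs.** 250 per arm (2.1); two-sided alpha 0.05/3 = 0.01667, critical value 2.394 (8.1); drop-out 10% per six months (8.1); failures from month 12 (8.1); two years of follow-up after the last patient (1.2, 8.1); accrual of three years (1.2) or four (3.1), assumed uniform.

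**Formulas.** Time is in six-month units. With L = -ln(1 - p) for failure, d = -ln(0.9) = 0.1054 for drop-out, start s, and follow-up T uniform on 4-10 units (three-year accrual) or 4-12 (four-year):

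- P(event) = exp(-d·s) · L/(L+d) · [1 - mean of exp(-(L+d)(T-s))]
- D = 250 · (P1 + P2), HR = ln(1-p2)/ln(1-p1)
- Power = Φ(|ln HR| · √(D/4) - 2.394)

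**Step 1: the plan's own figure, 10% v 5%, s = 2, three-year accrual.**

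- 10% arm: L = 0.1054; 0.81 × 0.5 × (1 - 0.3724) = 0.2542.
- 5% arm: L = 0.0513; 0.81 × 0.3274 × (1 - 0.4739) = 0.1395.
- D = 250 × 0.3937 = 98; HR = 0.0513/0.1054 = 0.487; |ln HR| = 0.720.
- Power = Φ(0.720 × 4.96 - 2.394) = Φ(1.18) = 88%.

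The second model counts failures at six-monthly visits, the first at month 12. The chance of failing at visit k (k = 2, 3, ...) is 0.9^k (1-p)^(k-2) p, averaged over follow-up.

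| Contrast | Model | 3-year accrual: events, power | 4-year accrual: events, power |
|---|---|---|---|
| 10% v 5% (HR 0.487) | continuous hazard | 98, 88.0% | 108, 91.0% |
| 10% v 5% | six-monthly visits | 110, 91.7% | 119, 93.8% |
| 20% v 12% (HR 0.573) | continuous hazard | 180, 91.0% | 192, 92.8% |
| 20% v 12% | six-monthly visits | 199, 93.7% | 210, 94.9% |

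Seven of the eight cells are at or above 90% and the eighth is 2 points below. The stated power against metformin is essentially reproduced.

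**Step 2: lifestyle versus rosiglitazone.** The formula and alpha are unchanged. The protocol gives no rates for this pair, so the following are illustrative. Example, 5% v 7.5%, s = 2, three-year accrual: D = 250 × (0.1395 + 0.1997) = 85; HR = 0.658, |ln HR| = 0.419; power = Φ(0.419 × 4.60 - 2.394) = Φ(-0.47) = 32%.

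| Rates per six months | Power: failures from month 12, 3-year accrual | Power: failures from month 0, 4-year accrual |
|---|---|---|
| 5% v 6% | 6% | 9% |
| 5% v 7.5% | 32% | 52% |
| 5% v 2.5% | 57% | 82% |
| 12% v 15% | 19% | 30% |

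A start at month 6 falls between the two columns. The right-hand column is more generous than the protocol's own start of failures.

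The six-monthly visit model (month 12, three-year accrual) shows how power falls as the second arm improves on metformin:

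- One arm at 5%, the other at 10 / 9 / 8 / 7.5 / 7%: 92 / 76 / 51 / 36 / 23%.
- One arm at 12%, the other at 20 / 18 / 16 / 15 / 14%: 94 / 74 / 38 / 21 / 10%.
- Equal rates: the rejection probability is alpha, 1.7%.

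**Step 3: detectable difference.** HR = exp(-2(2.394 + z)/√D), with z = 1.282 for 90% power and 0.842 for 80%. If both arms run near 5%, this pair yields about 79 events (visit model, three-year accrual), so the detectable HR is 0.44 at 90% power and 0.48 at 80%. Near 12% there are about 164 events, giving 0.56 and 0.60. For 90% power, the two active arms would have to differ from each other by slightly more than each was planned to differ from metformin (0.487 and 0.573).

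**The case against.** The best defense is that 2.1 means only that alpha has been set aside for all three tests, and Bonferroni over three pairs does that correctly. Section 8.1 also plans for a reduction in one of the intensive groups; if only one works, the third pair has the same contrast as the comparison with metformin and about 92% power. The intermediate contrasts above are not the protocol's, and it never claims 90% for them.

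Much of this stands. Alpha control is sound, and the third pair does have high power in the one-arm-works case. But the sentence in 2.1 states the significance level separately, so its power claim says something more, and no such condition is attached to it.

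A reader might go further and infer that the 90% against metformin is itself not delivered, because the rate is described as HbA1c over the threshold while the endpoint needs six months of confirmation. The documents do not support that. Section 8.1 opens by defining failure as the persistent elevation (or inability to wean from insulin) and lists a treatment failure rate from the first annual visit as the input. Figures of 73-80% for 10% v 5% arise only by adding a confirmation lag on top of that month-12 start, which may count the delay twice. Lower figures need a share of crossings that persist, and the protocol gives none. What remains is loose wording and an unclear source for the 10-20% rate.

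**Conclusion.** The point holds for the third comparison. Section 2.1 claims power for lifestyle versus rosiglitazone that 8.1 does not supply. At the planning rates it is about 90% only if one of those arms is no better than metformin. If both work, it runs from 6-9% (5% v 6%) through 32-52% (5% v 7.5%) to 57-82% even when one arm halves the other's 5% rate; 12% v 15% gives 19-30%. These figures rest on illustrative rates, constant hazards after the start of failures, uniform accrual and the protocol's drop-out.

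The claim of at least 90% against metformin should not be called wrong. The accrual contradiction is real but small: for 10% v 5% on a continuous hazard it moves power from 88% to 91%, on either side of the stated figure. This is a correction to a stated design property and no ground for changing the design.

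**What to change.** In 2.1, restrict the statement about power to each combination arm versus metformin. Add that lifestyle versus rosiglitazone is tested at the same adjusted alpha with lower power, and give its detectable hazard ratio (on the working above, about 0.44 for 90% power if both arms run near 5% per six months, and 0.56 near 12%).

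In 8.1, replace the threshold wording in the power statements with confirmed treatment failure. Reconcile the accrual period between 1.2 and 3.1, and state the power for the chosen period and event model. For 10% v 5% with failures from month 12, that is 88% (three years) or 91% (four years) on a continuous hazard, and about 92% or 94% counting failures at six-monthly visits.

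The cost is text only, with no added patients, visits or analyses. The protocol gives up a claim for the third pair that its calculation does not support.

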## 2.2 Secondary

There are a number of secondary outcomes in this trial. The results of these secondary outcomes help interpret the primary effect of the treatment regimens on HbA1c. These secondary aims have been chosen because they provide insight into the mechanism by which the treatment regimens affect durable glycemic control (e.g., effects on insulin resistance, sensitivity, diet and physical fitness) or because they provide information concerning the differential risks and benefits of the three treatment arms (e.g., studies of microvascular complications and cardiovascular risk). Data are collected from the child, the biological parents, and a designated family support person, or FSP, who participates in the intervention with the child (may be the same as the child's parent or guardian). The following sections describe the various outcome measures selected for the TODAY trial.

### 2.2.1 Glycemic Control

Mean HbA1c levels for the three treatment arms are compared throughout the trial as measures of the degree and durability of glycemic control. The overall goal is to maintain HbA1c levels as close to the normal range as possible in order to reduce long-term diabetes complications. During the trial, the investigator and the participant are blinded to HbA1c results. However, both are informed if (1) HbA1c  $\geq 8\%$ , (2) HbA1c is between 6-8% and has increased  $\geq 0.8\%$  (as determined by a difference from the prior visit value), or (3) HbA1c is at the target of  $\leq 6\%$ . This alert system allows clinicians to work with participants and families to reinforce adherence with the treatment protocol and to ensure safety.

In order to gain greater insight into possible differences in glycemic control between the treatment arms and to provide greater understanding of the durability or loss of targeted glycemic control, data are collected regarding daily fingerstick blood glucose readings.

Participants are taught self-monitoring of blood glucose levels and obtain blood glucose readings two times per day—in the morning on awakening (fasting) and one additional time (e.g., before dinner, lunch, two hours after dinner) each day. Additional testing is recommended during periods of illness. At all clinic visits, meters are downloaded; the number of tests performed per day as well as the 14-day and 30-day average glucose levels are recorded and compared for the three treatment arms.

In addition, participants are asked to obtain home glucose levels fasting and two hours following lunch and dinner for two days of the week before each clinic visit. Values are analyzed for mean fasting and postprandial levels and with regard to the incidence of postprandial hyperglycemia.

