#### 4.2.1.2 Rosiglitazone

Patients who are randomized to metformin plus rosiglitazone treatment group are started on a dose of 2 mg rosiglitazone bid. After 8 weeks, the dose is increased to 4 mg bid. Patients who reach the primary endpoint and begin add-on insulin therapy (see section 4.7) have the rosiglitazone dose lowered to 2 mg bid.

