#### 4.7 Add-on Insulin Therapy

- *Failure to maintain adequate metabolic control:* If HbA1c  $\geq$  8.0%, therapy is re-invigorated by more frequent telephone contact and visits. If HbA1c remains  $\geq$  8% throughout the next six months, then the patient is classified as failing to maintain

adequate metabolic control and *if* the participant's fasting blood glucose values are not in target then add-on therapy with insulin is initiated.

- *Outcome assessments before the initiation of add-on insulin therapy:* Before starting insulin treatment, participants undergo a comprehensive outcomes assessment unless this has been completed within the past three months.
- *Add-on insulin treatment regimen:* Patients who meet criteria for add-on insulin therapy continue to take the study drug metformin but discontinue the study drug rosiglitazone. The patients and clinicians remain masked to the treatment assignment but are unmasked to HbA1c. Initial insulin treatment is glargine insulin, 0.2 units per kilogram given in the evening. The dose is increased up to 1.0 U/kg/day (to a maximum of 100 units), until fasting blood glucose (FBG) values between 70-150 mg/dL are achieved.  
Add-on glargine insulin therapy is considered unsuccessful if (1) 1.0 U/kg/day (to a maximum of 100 units) does not bring FBG to target within 1 month or (2) HbA1c > 8% at 3 months or (3) HbA1c > 7% at 6 months. At that point, insulin therapy—including adding rapid, short, or intermediate acting insulin—is provided at the clinician's discretion.
- *Self-monitoring of blood glucose (SMBG):* During insulin therapy, patients are asked to monitor blood glucose levels at least four times a day. Target fasting glucose and pre-meal glucose is 70-150 mg/dL and the target peak postprandial glucose is  $\leq 200$  mg/dL.

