- *Temporary use of insulin:* Some patients may require temporary suspension of study drug and use of insulin. This is referred to as 'on leave' and may be due to (1) temporary medical conditions such as hospitalization or intercurrent illness (see chapter on safety), (2) a sexually active female not on appropriate contraception, or (3) pregnancy (see section on pregnancy below). While 'on leave', patients and clinicians remain masked to study drug and TLP activities are modified as needed by the intervention team. The patient continues to attend quarterly visits but HbA1c outcome measurement is discontinued during temporary use of insulin, except during pregnancy and nursing when A1c is measured for clinical care. Any case in which the participant has been on temporary insulin therapy for  $\geq 2$  weeks must be reviewed by the Protocol Review Committee. If the participant has been off study medications for  $\geq 1$  month, study procedures associated with an annual visit are not collected until the patient is back on study treatment (drug and/or TLP) for an adequate time period.  
Any type or dose of insulin can be used at the discretion of the treatment team. In such cases, an attempt is made to withdraw insulin once the acute event has resolved and study drugs are resumed. In the case of pregnancy, participants are weaned over a 3 month period once pregnancy and lactation are complete. In the case of a temporary medical condition such as hospitalization or intercurrent illness, weaning occurs over 2 weeks if the event lasted 2 weeks or less; if the event lasted more than 2 weeks, weaning occurs over 1 month. Withdrawal of insulin occurs regardless of blood glucose values; if metabolic decompensation occurs, appropriate safety procedures are followed (see next bullet for details).
- *Metabolic decompensation:* Metabolic decompensation is defined as hyperglycemia (BG > 300 mg/dL) accompanied by significant symptoms (e.g., vomiting, dehydration, lethargy) and/or moderate or large urinary ketones, or sustained hyperglycemia during home glucose monitoring [80% of BG tests are > 300 mg/dL (non-fasting) or > 200

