Life-table analysis assesses the risk of the first event in time. Some processes, however, involve recurrent events such as the back-and-forth between elevated and normal blood pressure. For these recurrent events, the family of statistical models based on the theory of counting processes are applied [Fleming and Harrington 1991].

Longitudinal data analysis techniques are used to analyze repeated measures data (e.g., glycemia, fasting lipids, blood pressure, physical activity, quality of life). These include: (1) analyses of the point prevalence of a discrete characteristic (e.g., hypertension) at successive repeated visits over time [Lachin and Wei 1988]; (2) multivariate rank analyses of quantitative (e.g., 2 hour OGTT) or ordinal (e.g., the Child Health Questionnaire subscales) measures over successive visits [Wei and Lachin 1984]; (3) the parametric linear random effects model of Laird and Ware [1982] to compare participant slopes over time (e.g., rate of change in fasting glucose) under linearity and normality assumptions; and (4) techniques developed by Liang and Zeger [1986] to compare participant slopes under a generalized linear models framework.

- *Interim analysis:* The Lan-DeMets [1983] spending function approach is used to adjust the probability of a type I error for testing the primary outcome when interim ‘looks’ of the data are taken by the Data Safety Monitoring Board. The spending function corresponding to an O’Brien and Fleming [1979] boundary are used. The Lan-DeMets procedure is flexible, in that the number of looks does not have to be specified in advance and the time interval between looks does not have to be the same throughout TODAY. The rate at which the type I error is spent is a function of the fraction of total information available at the time of the interim analysis (i.e., information time). For an interim analysis using the logrank test (i.e., time to confirmed treatment failure), the information time is the fraction of the total number of confirmed treatment failures to be accrued in the entire TODAY. Since the total number of failures to be accrued is unknown, an estimate of the information time is based on the fraction of total patient exposure [Lan and Lachin 1990].

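### The all-visit HbA1c comparison is read as durability of control, but after treatment failure it reflects the assigned regimen plus protocol insulin

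*Protocol*

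**What the plan says.** **Outcome.** Protocol 2.2.1: "Mean HbA1c levels for the three treatment arms are compared throughout the trial as measures of the degree and durability of glycemic control". Section 2.2 says the secondary outcomes serve to interpret the primary effect on HbA1c.

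**Analysis.** Section 8.2 makes intent-to-treat, in all randomized patients by assigned arm, the principal approach for secondary as well as primary outcomes. It assigns glycemia to repeated-measures methods. One of the four it lists is a linear random-effects model "to compare participant slopes over time (e.g., rate of change in fasting glucose) under linearity and normality assumptions".

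**Data collection.** The table in 5.1 keeps HbA1c on a quarterly and annual schedule after year 1, with no stop at the primary outcome.

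**Insulin after failure.** Section 4.7 classifies a patient as failing when HbA1c stays at or above 8% for six months. If the patient's "fasting blood glucose values are not in target then add-on therapy with insulin is initiated". The dose is raised "until fasting blood glucose (FBG) values between 70-150 mg/dL are achieved". Add-on glargine counts as unsuccessful, and other insulin may follow, if that target is missed or if "HbA1c > 8% at 3 months or (3) HbA1c > 7% at 6 months". Patients and clinicians are unmasked to HbA1c at this stage. A comprehensive outcomes assessment comes before insulin unless one was done in the previous three months.

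**The only stated suspension.** For patients on leave, "HbA1c outcome measurement is discontinued during temporary use of insulin", with an exception for clinical care in pregnancy and nursing. Section 4.7 has no matching rule for add-on insulin.

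**The concern.** Durability of control invites the question of how long each assigned regimen holds glycemia. Once a failing patient starts insulin aimed at fasting glucose and adjusted on HbA1c, both measures respond to the rescue as well as to the regimen. The arm that fails more has more of its worst values lowered in this way, so a late comparison of means moves toward no difference. A fasting-glucose path that rises to failure and turns down when insulin starts also breaks the linearity that the slope model assumes.

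What is at stake is interpretation. A real benefit on time to failure could be accompanied by similar late HbA1c means and be misread as inconsistent or short-lived. The pull is stronger the more the arms differ in failure.

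**Working it through.** **1. The plan's own figure.** Section 8.1 claims at least 90% power for the primary comparison. It gives no figure for HbA1c or fasting glucose.

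- Inputs: 250 per arm; 10% vs 5% or 20% vs 12% failing per six months; 10% dropout per six months; α = 0.05/3 = 0.0167 two-sided (8.1). Three years of accrual and two of further follow-up (1.2).
- Reading adopted: failures accrue over the six months that end at the first annual visit.
- Hazard ratios: ln 0.95 / ln 0.90 = 0.487 and ln 0.88 / ln 0.80 = 0.573.
- Schoenfeld power = Φ(½ √events × |ln HR| − z), with z = 2.394. With 122.4 events the power is 0.944; with 218.3 events it is 0.957.

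The claim reproduces on this reading. With no failures before month 12 it would be 0.880 and 0.910. The four-year recruitment period in 3.1 would raise those to 0.910 and 0.928.

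**2. Share already failed.** Ignoring dropout, share = 1 − (1 − p)^k, with k = (m − 6)/6 at month m.

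| Month | k | 10% vs 5% | 20% vs 12% |
|---|---|---|---|
| 24 | 3 | 27% vs 14% | 49% vs 32% |
| 36 | 5 | 41% vs 23% | 67% vs 47% |
| 60 | 9 | 61% vs 37% | 87% vs 68% |

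For example, 1 − 0.90⁵ = 0.410 and 1 − 0.95⁵ = 0.226. If no failures occur before month 12, k = (m − 12)/6 and the month-36 shares are 34% vs 19% and 59% vs 40%. Because add-on insulin also requires fasting glucose out of target, these shares are upper bounds on its use among HbA1c failures.

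**3. Effect on the month-36 mean difference (10% vs 5%).** The protocol gives no HbA1c SD, no gap between failures and non-failures, and no response to insulin. Assumed here: a gap of 2.5 points; a fall on insulin of 0.5, 1.0 or 1.5 points; every failure on insulin.

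- Failure-driven difference without insulin = (0.410 − 0.226) × 2.5 = 0.46 points.
- With insulin = (0.410 − 0.226) × (2.5 − fall) = 0.37, 0.27 or 0.18 points.
- Fraction lost = fall / gap = 20%, 40% or 60%. It scales with the share of failures given insulin: if only half were, the loss would be 10% to 30%.

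**4. Illustrative power.** Assume SD 1.5, two-sided α = 0.05 and 250 × 0.9⁶ = 133 per arm. Power for the month-36 comparison falls from 0.70 to 0.51, 0.32 or 0.17.

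**The case against.** **The target is legitimate.** Section 2.2.1 speaks of treatment arms and goes on to say that HbA1c should be kept near normal to limit long-term complications. HbA1c under the regimen and whatever insulin follows is relevant to that, and intent-to-treat is the stated principle. This stands: the all-visit comparison should remain. What does not survive is presenting it, unqualified, as a measure of durability.

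**Durability is already the primary outcome.** Time to failure is reached before add-on insulin starts. This also stands. A reader might infer that the primary result is diluted; it is not.

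**This belongs in the analysis plan.** Detail on post-insulin values could be left there. But the protocol itself fixes the comparison across the whole trial, in all randomized patients, with HbA1c still collected after failure, and attaches the durability reading to it.

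**Stronger readings that the text does not support.** A reader might infer that fasting glucose is also compared over the whole trial, or that HbA1c slopes are biased by some definite percentage. The phrase in 2.2.1 covers mean HbA1c only. The fasting-glucose slope in 8.2 is an example, conditioned on linearity, and 8.2 names no slope model for HbA1c. Other methods listed there need no linear path. Nor does the suspension of HbA1c during temporary insulin show that the protocol recognised this problem: those patients have study drug suspended, whereas failures stay on study metformin.

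**The remedy has its own weakness.** Treating later values as missing at random is plausible when failure is triggered by observed HbA1c. It is weaker for patients who cannot be weaned from temporary insulin, because that failure rests on symptoms or ketones and HbA1c outcome measurement has been suspended. This stands and shapes the fix.

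**Conclusion.** The point holds in a limited form. Read as durability of the assigned regimen, the late HbA1c comparison is diluted toward no difference if insulin lowers glucose and the arms fail at different rates. A fasting-glucose slope fitted through the start of insulin breaks its own linearity assumption.

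The planning rates imply that the worse arm has 13 to 24 percentage points more failures between months 24 and 60, counting failures from month 6. The 20% to 60% loss and the power figures are illustrations that rest on the assumed gap, fall, SD and full uptake of insulin; the document does not fix the true size. The matter is one of labelling plus one added analysis, and is worth changing because the change is cheap.

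**What to change.** 1. In 2.2.1 and 8.2, keep the all-visit intent-to-treat comparison and label it as assigned regimen followed by protocol insulin.
2. Add a prespecified durability analysis of HbA1c and fasting glucose: a likelihood-based mixed model on scheduled values up to and including the pre-insulin primary-endpoint assessment.
3. Add a sensitivity analysis that does not treat failure as ignorable, in particular for failure-to-wean cases whose HbA1c outcome measurement was suspended.
4. Reconcile the two statements on rosiglitazone after failure, since they decide what the post-failure values represent in that arm. Section 4.7 says patients "continue to take the study drug metformin but discontinue the study drug rosiglitazone". Section 4.2.1.2 says those who reach the primary endpoint and "begin add-on insulin therapy (see section 4.7) have the rosiglitazone dose lowered to 2 mg bid".

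The cost is wording, one extra model with its sensitivity analysis, and reliance on missing-at-random in the main durability model. The data are already scheduled for collection.
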